### Participant screening and selection

2.2

The diagnosis of LAGC will be established based on the Chinese Society of Clinical Oncology guidelines for GC (2024). Pathological classification will follow the World Health Organization Classification of Digestive System Tumors, 5th edition, and tumor staging will adhere to the AJCC Cancer Staging Manual, 8th edition. Potentially eligible patients meeting these diagnostic criteria will be systematically assessed against the specific inclusion and exclusion criteria detailed below. Patients who fail to meet all inclusion criteria or meet any exclusion criterion will not be enrolled in the study.

#### Inclusion criteria

2.2.1

Histologically or cytologically confirmed adenocarcinoma of the stomach or gastroesophageal junction.Resectable or potentially resectable disease with a clinical stage of cT1-2bN1-3M0, cT3-4bN0M0, or cT3-4aN1-3M0 (Stage II–III).Previous anti-tumor treatment, including chemotherapy, radiotherapy, immunotherapy or targeted therapy, is not permitted;Adequate organ function, defined as:• Absolute neutrophil count ≥ 1.5 × 10^9^/L• Hemoglobin ≥ 9.0 g/dL• Platelet count ≥ 80 × 10^9^/L• Serum albumin ≥ 30 g/L• Serum total bilirubin ≤ 1.5 × upper limit of normal (ULN)• Aspartate aminotransferase and alanine aminotransferase ≤ 2.5 × ULN• Alkaline phosphatase ≤ 2.5 × ULN• Serum creatinine ≤ 1.5 × ULNKarnofsky Performance Status score ≥ 70.Age between 18 and 75 years.Willing and able to provide written informed consent.

*Potentially resectable disease is defined, as clinical stage II–III disease, according to CSCO gastric cancer guidelines and multidisciplinary team (including surgical oncologists and radiologists) assessment, including tumors considered technically unresectable at diagnosis but potentially convertible to R0 resection following neoadjuvant therapy.

#### Exclusion criteria

2.2.2

Evidence of distant metastasis.Known hypersensitivity or contraindication to fluorouracil, oxaliplatin, or any component of the investigational Chinese herbal product.Combined with other parts of the primary malignant tumor. Subjects without disease for 5 years, or with a history of completely resected non-melanoma skin cancer or successfully treated carcinoma *in situ* were eligible for the study;Acute gastrointestinal complications such as complete/incomplete obstruction, active bleeding, perforation, or dysphagia that would preclude oral intake.Pregnancy or lactation. Patients with severe neurological, psychiatric, or cognitive disorders that would impair compliance or consent.Significant cardiac disease within 6 months prior to enrollment, including uncontrolled angina, arrhythmia, congestive heart failure, myocardial infarction, or cardiac insufficiency.Any other concurrent severe acute or chronic medical or psychiatric condition, or laboratory abnormality that, in the investigator’s judgment, would increase the risk associated with study participation or interfere with the interpretation of study results.Legal incompetence or any other condition rendering the patient unsuitable for study participation.

#### Criteria for discontinuation of study intervention

2.2.3

Occurrence of an adverse event or intercurrent illness preventing the completion of at least 4 treatment cycles.Voluntary withdrawal of informed consent by the subject.Pregnancy during the study or loss to follow-up.

#### Criteria for study withdrawal

2.2.4

Subject’s request to withdraw from all study-related procedures.Poor protocol compliance as judged by the investigator.Termination of the study by the sponsor.Regulatory mandate to halt the trial.Any other reason deemed necessary by the investigator for the subject’s well-being or the integrity of the study.

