#### Management of discontinuations/withdrawals

2.2.5

The investigator will make every reasonable effort to retain participants in the study and on the assigned treatment, unless discontinuation is considered to be in the subject’s best interest. For any subject who discontinues the study intervention or withdraws from the study, the investigator will attempt to perform and document an end-of-treatment assessment.

For participants who discontinue study intervention due to an adverse event or toxicity, safety follow-up will continue for at least 28 days after the last dose of study medication (or until resolution or stabilization of the AE, whichever is longer). All AEs occurring during this period will be recorded and graded. For participants who withdraw consent or are lost to follow-up without an ongoing AE, only survival follow-up will be performed as described above. Survival follow-up will be conducted every 3 months (telephone contact is permissible) until the occurrence of a study endpoint event.

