### Statistical analysis

2.9

All analyses will be performed using SAS software (version 9.4). Efficacy analyses will be conducted on both the Full Analysis Set (intention-to-treat principle) and the Per-Protocol Set. Safety analyses will be performed on the Safety Set. Prespecified subgroup analyses based on randomization stratification factors, and multivariable adjustment will be used to minimize the influence of treatment heterogeneity. Time-to-event endpoints (EFS, DFS, OS) will be summarized using Kaplan-Meier survival curves and compared between groups using the log-rank test. The Cox proportional hazards model will be employed for multivariate analysis to adjust for potential confounding variables. All statistical tests will be two-sided, with a *p*-value < 0.05 considered statistically significant.

Subgroup analyses: To explore potential beneficiary characteristics, we will perform prespecified subgroup analyses according to baseline clinical factors (age, sex, tumor clinical stage, T stage, N stage, PD-L1 CPS, MSI/MMR status, chemotherapy regimen, immunotherapy use, baseline Karnofsky score, TCM syndrome classification, and relevant biomarker subgroups). For each subgroup, the treatment effect on EFS will be estimated, and interactions between treatment and subgroup factors will be tested using the Cox model. The model selection strategy will be forced entry of these pre-specified variables (no stepwise selection) to avoid overfitting and multiplicity issues. Proportional hazards assumption will be tested using Schoenfeld residuals. These analyses are exploratory and hypothesis-generating; no adjustment for multiple testing will be applied. This study is not powered for formal predictive model development or validation.

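### Section 2.2.4 lets investigators withdraw poorly compliant patients from the study, and no scheduled EFS tumour assessment is assigned to them afterwards

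*Protocol article*

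**What the plan says.** The protocol separates stopping the intervention (2.2.3) from leaving the study (2.2.4). Among the reasons for leaving the study is "Poor protocol compliance as judged by the investigator". No threshold is attached. A second discretionary reason follows: "Any other reason deemed necessary by the investigator for the subject’s well-being or the integrity of the study".

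Section 2.2.5 opens with a retention commitment: "The investigator will make every reasonable effort to retain participants in the study and on the assigned treatment", subject to the patient's interest. For anyone who discontinues or withdraws, "the investigator will attempt to perform and document an end-of-treatment assessment"; its content is not given. Two groups then receive a follow-up rule. Those stopping for an adverse event or toxicity have safety follow-up. For the others named, "For participants who withdraw consent or are lost to follow-up without an ongoing AE, only survival follow-up will be performed as described above". That contact is described as follows: "Survival follow-up will be conducted every 3 months (telephone contact is permissible) until the occurrence of a study endpoint event". Patients withdrawn for poor compliance are in neither group.

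Footnote 2 of Table 1 gives three routes into the regular follow-up phase: completing perioperative treatment, progression, and intolerable toxicity. Section 2.1 says that all patients are followed for three years. Section 2.7.1 defines EFS by progression that rules out curative surgery, recurrence, or death. On analysis, section 2.9 states: "Efficacy analyses will be conducted on both the Full Analysis Set (intention-to-treat principle) and the Per-Protocol Set".

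**The concern.** An intention-to-treat analysis of EFS needs the endpoint to be sought in every randomised patient, whatever happened to treatment. Here a judgement about compliance can end a patient's participation, and the text then assigns no imaging to find recurrence. A telephone contact about survival will find deaths but will not reliably date recurrence. A statistical analysis plan can set censoring rules, but it cannot recover recurrence dates that were never collected, so this belongs to trial conduct.

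Patients who fall behind with a thrice-daily oral product during chemotherapy may well be those with a worse outlook. If so, their removal leaves a healthier group at risk. If it happens more often in one arm, the EFS comparison moves in that arm's favour. The withdrawal is also unnecessary: the Per-Protocol Set already deals with non-compliance, and section 2.7.2 plans to report patients with adherence below 80% as a category.

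**Working it through.** **1. The passages side by side**

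| Reason for stopping or leaving | Follow-up assigned |
|---|---|
| Treatment completed, progression, intolerable toxicity | Regular follow-up phase (Table 1, footnote 2) |
| Adverse event or toxicity | Safety follow-up for at least 28 days (2.2.5) |
| Consent withdrawn, or lost to follow-up | Survival contact only (2.2.5) |
| Poor compliance (2.2.4) | Attempted end-of-treatment assessment; nothing further named |

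The last row cannot be squared with follow-up of all patients for three years (2.1).

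**2. The plan's own figures (2.5)**

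- Inflation for dropout: 114 / (1 − 0.20) = 142.5, rounded up to 143 per group, 286 in total. This reproduces.
- 20% of 286 is about 57 patients. This is an allowance for all dropout; compliance withdrawal is an unquantified part of it.
- Exponential hazards per month: control −ln(0.44)/36 = 0.0228; experimental −ln(0.64)/36 = 0.0124; hazard ratio 0.544.

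**3. Is power the problem?**

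With 36 months of accrual and 60 months in total, the event probability is 1 − (e^(−24λ) − e^(−60λ)) / (36λ), which averages 0.503 over the two arms. That gives 0.503 × 286 ≈ 144 events, or 0.503 × 228 ≈ 115 with 114 per arm. About 85 (Schoenfeld) to 90 (Freedman) are needed for 80% power. Lost events threaten power little; the issue is bias.

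**4. Effect on the comparison when there is no true effect**

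Assumptions, none from the documents:
- In each arm 20% of patients have k times the average hazard λ = 0.0228. The rest have λ(1 − 0.2k)/0.8, which is 0.75λ for k = 2 and 0.5λ for k = 3.
- All withdrawals come from the high-risk patients, at 6 months, with no EFS ascertainment afterwards.
- 143 per arm, log-rank test, 3,000 runs per row. HR is the geometric mean over runs of the ratio of events per person-time.

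Monte Carlo standard error at 5% is √(0.05 × 0.95 / 3000) ≈ 0.4 points.

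| Withdrawn, experimental vs control | HR, k = 2 | HR, k = 3 | Two-sided type I error, k = 2 | k = 3 |
|---|---|---|---|---|
| 0% vs 0% | 1.00 | 1.00 | 4.8% | 5.2% |
| 10% vs 10% | 1.00 | 1.00 | 5.8% | 5.1% |
| 5% vs 10% | 1.03 | 1.05 | 5.2% | 5.9% |
| 15% vs 5% | 0.93 | 0.89 | 6.8% | 9.4% |
| 20% vs 5% | 0.90 | 0.84 | 10.2% | 14.8% |

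If withdrawal is unrelated to risk (k = 1), HR stays near 1.00 and error near 5% in every row.

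**5. Effect on the Kaplan-Meier level at 36 months**

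Assume a share w withdraws at a time uniform over 0 to 9 months and has k times the hazard b of the rest. Choose b so that w·e^(−36kb) + (1 − w)·e^(−36b) equals the true 3-year EFS. Simulated with 200,000 per arm:

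| w | k | True 44% becomes | True 64% becomes | Apparent difference |
|---|---|---|---|---|
| 20% | 1.5 | 46.2% | 66.1% | 19.9 points |
| 20% | 2 | 48.4% | 67.7% | 19.3 points |
| 10% | 2 | 46.1% | 65.9% | 19.8 points |

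With no true effect, 15% vs 5% withdrawn at k = 2 gives 47.0% vs 45.2%, a spurious 1.8 points. Numerical integration of the same model agrees with all these levels to within about 0.3 points.

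**The case against.** Three stronger readings are tempting, and the documents support none of them.

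- A reader might infer that no tumour assessment is planned at all. But an end-of-treatment assessment is attempted, and the restriction "only survival follow-up will be performed as described above" is written for consent withdrawal and loss to follow-up, not for compliance. Telephone contact is allowed, not required. Contact runs until a study endpoint event, which could include recurrence. The text is silent or ambiguous for this group; it does not exclude assessment.
- A reader might infer that EFS is censored for outcome-related reasons. The article states no censoring rule, and one may stand in an analysis plan that is not shown. Nothing in the documents links compliance to prognosis.
- A reader might infer that the intention-to-treat analysis becomes impossible. All randomised patients can still be analysed as randomised, and deaths may still be captured.

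On size, the objection is also fair. The 20% allowance covers all dropout. The 2 to 4 point rise is a shift common to both arms and leaves the difference near 20 points. Distortion of the comparison needs an unequal split, which is assumed. Blinded investigators and a matched placebo (2.4, 2.6) make unequal judgement less likely, and the retention commitment should keep withdrawals few. Patients who have already progressed beyond curative surgery or recurred have their EFS event before any withdrawal matters.

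What remains is that blinding does not remove real differences in compliance between arms. The Discussion cites less gastrointestinal toxicity with the precursor formula, so the arms could differ, and the direction cannot be predicted. Ambiguity over whether randomised patients keep their primary-endpoint assessment is itself a defect in a protocol.

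**Conclusion.** The point holds as a conduct rule that can lose primary-endpoint data and that does not fit sections 2.1 and 2.9. The EFS analysis is put at risk of bias; it is not shown to be biased, and it is not undeliverable. The comparison is affected only if compliance withdrawal is both prognostic and unequal between arms. At an assumed 15% vs 5% the distortion is modest against the design hazard ratio of 0.544, but it is enough to lift the false-positive rate above the nominal 5%. It can also run against the product, as the 5% vs 10% row shows. This should be corrected, and correction is cheap: section 3 reports 61 patients recruited, so 286 − 61 = 225 are still to come.

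**What to change.** Remove poor compliance from section 2.2.4 as a reason to end study follow-up. Record it as a protocol deviation, to be handled in the Per-Protocol Set. Reconcile sections 2.1, 2.2.4 and 2.2.5 and footnote 2 of Table 1, so that every randomised patient stays on the scheduled EFS and survival assessments unless consent to follow-up is withdrawn. State that EFS events after non-compliance or after stopping the product count in the Full Analysis Set, and say whether the study endpoint event in 2.2.5 includes recurrence. Add a sensitivity analysis for patients whose EFS follow-up still ends early.

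This concerns data collection only. Decisions on stopping treatment, and the well-being criterion in 2.2.4, are left to the sponsor. The cost is protocol wording, a memo to sites and some extra follow-up visits; the sample size does not change. Patients who miss visits altogether may still be lost, and the change will not recover them.

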#### Management of discontinuations/withdrawals

2.2.5

The investigator will make every reasonable effort to retain participants in the study and on the assigned treatment, unless discontinuation is considered to be in the subject’s best interest. For any subject who discontinues the study intervention or withdraws from the study, the investigator will attempt to perform and document an end-of-treatment assessment.

For participants who discontinue study intervention due to an adverse event or toxicity, safety follow-up will continue for at least 28 days after the last dose of study medication (or until resolution or stabilization of the AE, whichever is longer). All AEs occurring during this period will be recorded and graded. For participants who withdraw consent or are lost to follow-up without an ongoing AE, only survival follow-up will be performed as described above. Survival follow-up will be conducted every 3 months (telephone contact is permissible) until the occurrence of a study endpoint event.

### Randomization method

2.3

The blinded document (Participant Randomization Table and Drug Assignment Table) of this trial is generated by unblinded statistician using SAS software (Version 9.4) and uploaded to the central randomization system by the randomization system administrator (provided by Beijing Bio-Thera Information Technology Co., Ltd). SAS software was used to generate random numbers and treatment groups corresponding to random numbers. Parameters such as procedure, seed number, block length during randomization were kept in an unblinded folder and the randomization table was reproducible. These persons were not involved in participant recruitment, treatment, or outcome assessment. The central randomization system will complete the assignment of participant randomization number and drug management during the trial. This trial was stratified by neoadjuvant chemotherapy ± immunotherapy using stratified block randomization. Authorized study personnel at each participating site performed subject assignment via the randomization system after confirming eligibility and obtaining informed consent. The grouping process was done automatically by a centralized system and did not rely on the subjective judgment of the researcher.

To ensure data confidentiality and prevent unauthorized access, the randomization system maintains a complete electronic audit trail documenting all allocation-related activities, including login attempts, randomization requests, data entries, and emergency unblinding, with timestamps and user identification. Access to the randomization module is strictly role-based, with different authorization levels assigned to investigators, study coordinators, statisticians, and system administrators. The integrity of the allocation process is further overseen by independent clinical monitors. The randomization schedule itself remains sealed and inaccessible to all study personnel until database lock, except for emergency unblinding.

### Blinding and emergency unblinding

2.4

The investigational product (SQFWG) and the placebo are identical in appearance, packaging, taste, and smell. All study medications will be manufactured, packaged, and supplied by Tiandi Hengyi Pharmaceutical Company. A unique randomization code will serve as the participant identifier. Subjects, investigators, caregivers, outcome assessors (including imaging evaluators), and data analysts will all be blinded to group assignment. Emergency unblinding of a participant’s treatment assignment via the central randomization system is permitted only if the investigator deems that knowledge of the treatment is essential for the clinical management of a serious adverse event. The system will automatically log all emergency unblinding requests and actions. The investigator must consult with the study’s principal coordinator and formally notify the trial sponsor within 24 hours following unblinding.

### Sample size calculation

2.5

This is a randomized, placebo-controlled superiority trial with a 1:1 allocation ratio. The primary endpoint is EFS. Based on the KEYNOTE-585 trial results (11), the assumed 3-year EFS rate for the control group (receiving perioperative chemotherapy ± immunotherapy) is 44%. We hypothesize that the addition of SQFWG will increase the 3-year EFS rate by 20% (absolute improvement), resulting in a rate of 64% for the experimental group. Using a two-sided significance level (α) of 0.05 and a power (1-β) of 80%, and assuming a constant accrual rate over an enrollment period of 36 months, the sample size was calculated using PASS software (version 15). This calculation yielded 114 participants per group. To account for an estimated 20% dropout rate, the final target enrollment is set at 143 participants per group. The design is event-driven, requiring a sample size of 286 cases. The duration of enrollment is 3 years, and the total study duration is 5 years, taking into account a 20% dropout rate.

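### The stated 114 per group for 80% power does not follow from the inputs in section 2.5 (they need about 84–90 without loss), and the design is called event-driven without an event target

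*Protocol article*

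**What the plan says.** Section 2.5 (Sample size calculation) takes a control 3-year EFS of 44%, adds 20 percentage points, "resulting in a rate of 64% for the experimental group", and sets a two-sided alpha of 0.05 and 80% power, "assuming a constant accrual rate over an enrollment period of 36 months". It then reports: "This calculation yielded 114 participants per group". This is raised to 143 per group for 20% dropout. Two further sentences complete the design: "The design is event-driven, requiring a sample size of 286 cases", and "The duration of enrollment is 3 years, and the total study duration is 5 years, taking into account a 20% dropout rate".

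Elsewhere, section 2.9 names the log-rank test for EFS. Section 2.1 says every patient is followed for 3 years. Section 2.8 places database lock after final participant follow-up. Section 3 gives recruitment from November 2025 to August 2028 and completion of the primary analysis in December 2030. The document contains no target number of EFS events.

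**The concern.** The power of a log-rank comparison is set by the number of events. Two survival rates, an accrual pattern and a study length fix both the required events and, under exponential survival, the patients needed to produce them. When the stated patient number is well above what those inputs require, either an input differs from the text or the power does.

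At stake is the planning statement for the primary endpoint. A reader will take the trial to have 80% power for a 20-point gain, when the design described has more. The smallest effect the trial can detect with 80% power is then also different from the one stated. This matters because section 4 itself calls the assumed effect large for an adjunctive herbal treatment. Separately, an event-driven design is analysed when a set number of events is reached. With no such number, the label conflicts with the calendar date given in section 3.

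**Working it through.** **Inputs (section 2.5, test from section 2.9).** 3-year EFS 44% and 64%; 1:1 allocation; two-sided alpha 0.05 (z = 1.960); power 80% (z = 0.842); uniform accrual R = 3 years; study length T = 5 years. Exponential survival is my assumption.

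**The plan's own figures.** The dropout step reproduces: 114/0.8 = 142.5, rounded up to 143, and 2 × 143 = 286. The 114 does not reproduce, as follows.

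**Hazards.** Control: −ln(0.44)/3 = 0.2737 per year. Experimental: −ln(0.64)/3 = 0.1488 per year. HR = 0.1488/0.2737 = 0.544; ln HR = −0.6095.

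**Events for 80% power.**
- Schoenfeld: 4 × (1.960 + 0.842)² / (ln HR)² = 4 × 7.849 / 0.3715 = 84.5, so 85.
- Freedman: 7.849 × [(1 + 0.544)/(1 − 0.544)]² = 89.8, so 90.

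**Probability of an event by 60 months.** P = 1 − [exp(−λ(T − R)) − exp(−λT)]/(λR).
- Control: 0.605. Experimental: 0.401. Mean: 0.503.

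**Patients per group.** 84.5/(2 × 0.503) = 84.0; 89.8/(2 × 0.503) = 89.2, so 90 as a whole number. The Lakatos method gives 85.4.

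**Other readings of the stated inputs, 80% power:**

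| Reading | Per group (Schoenfeld to Freedman) |
|---|---|
| 3 + 2 years, no loss | 84.0 to 89.2 |
| 3 + 2 years, 20% lost over 5 years | 89.9 to 95.6 |
| 3 + 2 years, 20% lost over 3 years | 94.0 to 99.9 |
| Fixed 3 years per patient, no loss | 91.9 to 97.6 |
| 3 years' accrual, then 3 years for all, no loss | 71.4 to 75.9 |
| Two proportions at 3 years | 97 (107 with continuity correction) |

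None gives 114.

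**What does give about 114.**
- A total of 4 years (12 months after last entry), Freedman: 114.2. The text says 5 years.
- A 5-year study with 20% loss per year, Schoenfeld: 115.7; with a loss hazard of 0.2 per year, 112.2. The text does not call the 20% annual, and inflating the result to 143 would then count dropout twice.

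**Power of the stated numbers at 60 months.**
- 114 per group, no loss: 228 × 0.503 = 114.7 events. Schoenfeld: √114.7 × 0.6095/2 − 1.960 = 1.30, power 90.4%. Freedman 88.6%, Lakatos 89.9%, simulated log-rank test (8,000 runs) 89.8%.
- 114 per group with 20% lost over 5 years: 86.4% (Freedman) to 88.4% (Schoenfeld). Over 3 years: 84.9% to 87.0%.
- 143 per group with 20% lost by 3 years: mean event probability 0.449, about 129 events, power about 93% (Schoenfeld).

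**Detectable effect with 115 events at 80% power.** HR = exp(−2 × 2.802/√115) = 0.593. The experimental 3-year EFS is then 0.44^0.593 = 61.5%, a gain of 17.5 points rather than 20.

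**The case against.** Several points on the other side are sound.

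The sentence describing the software run names the accrual period but not the follow-up. The 5 years appear later as the study length, and section 2.1 gives 3 years per patient. So 84–90 is one reading among several. This stands, but every stated reading falls short of 114.

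The 5-year sentence mentions the 20% dropout, so loss may have been built into the run. If it was 20% per year, 114 per group would have about 79–81% power (Schoenfeld). That is possible, but it is not stated, and the later step to 143 would apply dropout a second time. For the same reason, the 90% figure must be read as power without loss among the 114.

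A condensed article may leave the software module and its inputs to the full protocol. That is fair for the inputs. It does not cover a stated result that conflicts with the design stated beside it, or an event-driven label attached to a patient count.

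A reader might also infer that nothing fixes when the primary test is run, or that the analysis would fall at 85 events, near months 39–41. The document does not support either. Section 3 gives December 2030, section 2.8 ties database lock to final follow-up, and no section says the trial stops at 85 events. The conflict is between the label and that calendar rule.

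Nor does the discrepancy show an under-powered trial. It runs the other way.

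**Conclusion.** The point holds. Section 2.5 pairs 114 per group with 80% power, but the 5-year design it describes needs about 84–90 per group without loss, or 90–100 with 20% lost over 5 or 3 years. With 114 per group the power at 60 months is 89–90% without loss and about 85–88% with that loss. With all 286 and 20% lost by 3 years it is about 93% by Schoenfeld. These figures assume exponential survival, proportional hazards and uniform accrual.

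The likeliest explanation is an undisclosed follow-up or loss input, but the document does not show which. The error is conservative for the assumed effect, and neither the test nor its type I error is affected. It should be corrected because the stated power is not that of the stated design, and because the event-driven label conflicts with the calendar-based timing in sections 2.8 and 3. It does not threaten the trial's validity.

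**What to change.** Keep 286 patients. In section 2.5, state HR 0.544 and the follow-up and loss inputs actually used in PASS. Then choose one of two routes.

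(a) Keep the 5-year cut-off and drop the event-driven label. Restate power as about 90% without loss for 114 per group (about 115 events; HR detectable with 80% power about 0.59), or about 93% for all 286 with 20% lost by 3 years (about 129 events).

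(b) Keep the event-driven label and state the event count that triggers the primary analysis: 85–90 for 80% power, or 114–121 for 90% (Schoenfeld to Freedman). Give its expected calendar time and reconcile that with December 2030 in section 3.

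Either route costs a few sentences and, under (b), one number. No patients are added. Section 3 reports 61 recruited and no data analysis performed, so the change can still be made before any outcome is analysed.
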